## Abstract

**Background:**

Cigarette smoking among adults in the USA is a leading cause of preventable death worldwide, even though there has been a decline in prevalence since 2005. The addictive nature of nicotine is the chief reason smokers continue to use tobacco. Although the majority of smokers report a desire to quit smoking, a small minority who attempt to quit achieve long-term cessation. Combined, smoking cessation best practices include coordinated medication and behavioral treatments. However, these treatments are not currently adequately delivered to Medi-Cal beneficiaries in the publicly funded patient-centered medical homes (PCMHs) and community mental health clinics operated by Los Angeles County (LAC)-Department of Health Services (LACDHS) and LAC-Department of Mental Health (LACDMH).

**Methods:**

This is a 5-year implementation, cluster-randomized comparative effectiveness trial that will support the implementation of smoking cessation services delivered in LAC-LACDHS-operated outpatient primary care clinics and in LAC-LACDMH-operated community mental health clinics. We will enroll 1000 participants from clinics that will offer smoking cessation services and 200 from clinics that will offer treatment as usual. Participants will be asked to complete assessments at baseline, 3 months, 6 months, and 12 months. The assessments will include self-reports on smoking history, anxiety, stress, quality of life, and participant satisfaction. Participants who are assigned to clinics that provide smoking cessation services will also be asked about the frequency of their participation in the smoking cessation services during the 12-month period.

**Discussion:**

This study will evaluate the effectiveness and feasibility of implementing smoking cessation services in outpatient primary care and community mental health clinics. It will also determine if there will be higher rates of smoking cessation in the implementation sites as compared to the sites with treatment as usual. If the implementation proves to be effective, the plan is to sustain these services using a workflow we will develop in the LAC-operated sites. This would lead to ameliorating the significant smoking cessation treatment gaps among those served within the LAC Health Agency departments.

**Trial registration:**

ClinicalTrials.gov NCT04717544 “Embedding comprehensive smoking cessation programs into community clinics.” Registered on January 22, 2021

**Supplementary Information:**

The online version contains supplementary material available at 10.1186/s13063-022-06023-3.

## Administrative information

Note: the numbers in curly brackets in this protocol refer to SPIRIT checklist item numbers. The order of the items has been modified to group similar items (see http://www.equator-network.org/reporting-guidelines/spirit-2013-statement-defining-standard-protocol-items-for-clinical-trials/).

## Introduction

### Background and rationale {6a}

Tobacco use disorder is the leading cause of preventable death worldwide and is undertreated in the public sector. In 2018, the prevalence of current cigarette smoking among adults was 13.7% that was a significant decline from 2005 (20.9%) [1]. Additionally, cigarette use places an enormous burden on the US economy. From 2009 to 2012, smoking cost the USA between $289 and 332.5 billion (over that 3-year period) and between 46 and 53% of this is spent on adult medical care, while the rest is due to loss of productivity [2].

The prevalence of cigarette smoking is highest among adults who are male; aged 25–64 years, are American Indian/Alaska Native or multiracial; live below the federal poverty level; live in the Midwest or South; have a General Education Development (GED) certificate; are uninsured or insured through Medicaid; have a disability/limitation; are lesbian, gay, or bisexual; or have serious psychological distress [3]. Individuals with mental health and addictive disorders (MHAD) have higher rates of tobacco smoking and low rates of long-term smoking cessation, resulting in morbidity and mortality due to tobacco dependence [4, 5]. Barriers to treatment, such as inaccessibility to smoking cessation programs and medications, inhibit smoking cessation among those with comorbid MHAD and tobacco dependence [6]. Population-based interventions are critical to reducing the health and economic burden of smoking-related diseases among US adults, particularly among subpopulations with the highest prevalence of smokers.

The addictive nature of nicotine is the chief reason smokers continue to use tobacco. While about 70% of both adolescent and adult smokers state that they would like to quit smoking, only about 7% of smokers who try to quit on their own achieve long-term cessation each year [6]. There are a variety of treatment methods used to promote smoking cessation. A Cochrane database systematic review identified 12 treatment-specific reviews using pharmacological interventions for smoking cessation of which their analyses covered 267 studies, involving 101,804 participants [7]. The main outcome analyzed was smoking cessation although smoking reduction was also assessed. Some of the findings include that both nicotine replacement therapy (NRT) and bupropion were superior to placebo. Varenicline increased the odds of quitting compared with placebo. Head-to-head comparisons between bupropion and NRT showed equal efficacy. Varenicline was superior to single forms of NRT and to bupropion. Varenicline was more effective than nicotine patch, nicotine gum, and other NRT (inhaler, spray, tablets, lozenges), but was not more effective than combination NRT. Combined smoking cessation best practices include coordinated medication and behavioral treatments [2, 8, 9]. However, these treatments are not currently adequately delivered to Medi-Cal beneficiaries in the publicly funded PCMHs and community mental health clinics operated by LACDHS and LACDMH, respectively. With Los Angeles County being the second largest municipal health system in the nation, LACDHS and LACDMH serve 850,000 people annually. Of this population, 13% have tobacco use disorder (TUD) and tobacco-related disease attributes to one in seven deaths [10].

For these reasons, it is important to set up a comprehensive smoking cessation program in PCMHs and DMH clinics that will offer group counseling as well as medications for smoking cessation. We will conduct an implementation study of smoking cessation services delivered in LACDHS and LACDMH clinics lasting at least 5 years to determine if there will be higher rates of smoking cessation in the implementation sites compared to matched LAC-operated sites with treatment as usual (TAU).

### Objectives {7}

The aim of the present study is to create sustainable improved tobacco screening, treatment intervention, and cessation in LACDHS-operated outpatient primary care clinics and in LACDMH-operated community mental health clinics. This project will support the implementation of smoking cessation services delivered in LACDHS and LACDMH clinics and will evaluate the effectiveness and feasibility of these services. The primary outcome is to determine if there will be higher rates of smoking cessation in the implementation sites as compared with matched LAC-operated sites with TAU. Exploratory analysis will consider intervention effects on the smoking rate, such as smoking reductions. The primary aims of the current study are detailed below.

#### Primary aims

*Primary aim 1*: To test whether STUD participants have greater improvement in an objective measure of smoking behavior than TAU participants.

*Primary aim 2*: To test the penetrance of smoking cessation medications and counseling services in the STUDS arm vs. the TAU arm and between mental health and primary care clinics.

*Primary aim 3*: To test the dose effect on smoking cessation among those who receive medication and counseling services. Specifically, investigate if multiple medications plus counseling are more effective than single medication plus counseling, and what the dose-response effect of the number of counseling sessions on smoking abstinence.

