At the first interview, the researcher will explain the study and answer any questions participants may have. If they agree to participate in the study, they will be enrolled into the study at the first interview. The researcher will then set up a schedule to meet again at 3 months, 6 months, and 12 months. To enhance retention, participants will be asked to provide contact information for the research team to keep in contact for subsequent follow-up interventions.

At each interview, the researcher will complete brief medical and mental health assessments which will ask about participants’ overall physical and mental health, including their smoking status. Data will be collected in-person by the research team via computer-assisted interviews which will include self-reports on smoking history, anxiety, stress, quality of life, and participant satisfaction. Initially, at each interview, we planned on asking participants to complete the carbon monoxide (CO) breathalyzer test and provide a urine sample for the rapid dipstick cotinine test to determine the use of cigarettes and levels of nicotine in the body. The urine collected for this study was to be only tested for cotinine and no other substances. Breathalyzer and urine testing were temporarily suspended in March 2020 in response to the COVID-19 pandemic when enrollment and follow-up assessments shifted from in-person to telephone and in-person visits are not anticipated to resume. Prior to suspension, 12 participants in the TAU arm and 69 participants in the intervention arm completed CO and urine testing.

Participants who are assigned to clinics that provide smoking cessation services will also be asked about the frequency of their participation in the smoking cessation services during the 12-month period. Interviews will be conducted at the participating LAC outpatient clinic where participants receive their primary health care. The smoking cessation services will include a (1) weekly 60–75-min cognitive-behavioral therapy (CBT) smoking cessation counseling group which will be led by facilitators that have been trained through the Kick Ash program and may be a nurse, pharmacist, clinician, substance use disorder (SUD) counselor, behavioral health clinician, or counselor; and (2) smoking cessation medication that will be prescribed by a licensed, prescribing clinician. Smoking cessation medications will include varenicline (Chantix), bupropion (Zyban), and nicotine patches, gum, and lozenges.

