### Outcomes {12}

The primary outcome of the study is higher rates of smoking cessation in the intervention sites as compared with matched LAC-operated setting non-intervention sites. Exploratory analysis will consider intervention effects on the smoking rate, such as smoking reductions. To measure rates of smoking cessation, study participants will complete two objective measures collected at four time points at 3-month intervals within a 12-month period. Analysis will be at each time point compared to baseline. The objective measures include a carbon monoxide breathalyzer (piCO+Smokerlyzer) and a urinary rapid dipstick cotinine test (NicCheck) before March 2020. However, these measures were temporarily discontinued in response to COVID-19 when data collection shifted from in-person to telephone collection.

The study will evaluate the (1) penetrance of smoking cessation medications and counseling services, at intervention and non-intervention sites and between mental health and primary care clinics; (2) self-reported cigarette use, smoking urges, number of quit attempts, changes in self-reported anxiety, stress, quality of life, and participant satisfaction; (3) and the dose effect of medication and counseling services on smoking cessation.

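### Primary aim 1 and the Outcomes section still rest on objective smoking tests that stopped in March 2020, and no single primary time point is fixed

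*Protocol article*

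**What the plan says.** Primary aim 1 is "To test whether STUD participants have greater improvement in an objective measure of smoking behavior than TAU participants". The Objectives section puts the question more broadly: "The primary outcome is to determine if there will be higher rates of smoking cessation in the implementation sites". The Outcomes section ties that rate to biochemical tests: "To measure rates of smoking cessation, study participants will complete two objective measures collected at four time points at 3-month intervals within a 12-month period". It names the tests as exhaled CO and a urinary cotinine dipstick, and adds "Analysis will be at each time point compared to baseline".

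The same section then reports "However, these measures were temporarily discontinued in response to COVID-19 when data collection shifted from in-person to telephone collection". The Trial design section goes further: "in-person visits are not anticipated to resume". It also gives the extent of testing before the stop: "12 participants in the TAU arm and 69 participants in the intervention arm completed CO and urine testing".

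A workable definition of quitting appears only in the section on assessment and collection of outcomes, item 11. There it is self-report of no cigarettes over the preceding seven days, and CO corroboration is described as an initial plan. Model 1 in the section on statistical methods for primary and secondary outcomes compares values at study end.

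**The concern.** Neither aim 1 nor the Outcomes section was rewritten when testing stopped, and neither names a replacement measure. The Trial status section dates the current version January 16, 2021, about ten months after the suspension. So the document in force names a primary measure that is no longer collected.

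Two things are at stake. First, the blinding section says nobody is blinded. Moving from a biochemical test to self-report in an open trial therefore changes what a positive result would show, and the aim should say so. Second, the statements on timing compete, and an interim look at the number of participants who have stopped smoking is planned. With the measure and the visit both unsettled, the primary comparison could be chosen after outcome data have been seen.

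**Working it through.** **1. Coverage of the objective tests** (counts from Trial design, planned numbers from Sample size).

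- Overall: (12 + 69) / (200 + 1,000) = 81 / 1,200 = 6.75%.
- By arm: TAU 12 / 200 = 6.0%; intervention 69 / 1,000 = 6.9%.

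**2. Which visits those tests could cover** (dates from Trial status and Trial design). Recruitment opened on October 1, 2019, and testing stopped in March 2020. For a participant enrolled on the first day:

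- Month 3 falls on January 1, 2020. A month-3 test was possible for those enrolled by about the end of December 2019.
- Month 6 falls on April 1, 2020, after the stop. A month-6 test would have required an early visit.
- Month 12 falls on October 1, 2020, at least six months after the stop. No month-12 test was possible unless testing resumed.

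The article does not say at which visit the 81 were tested, so some or most of the tests may be baseline tests in current smokers.

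**3. The plan's power figure, and the same calculation on the tested subset.** Inputs from Sample size: 25% versus 5% abstinence, ICC 0.05, 14 and 3 clinics, 50% dropout, two-sided 5%, stated power 99.4%. Equal clinic sizes within each arm are assumed. Effective n = n / [1 + (m − 1) × 0.05], where m is the number per clinic.

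- Completers, intervention: m = 500/14 = 35.7, effective n = 182.8. TAU: m = 100/3 = 33.3, effective n = 38.2.
- Unpooled SE = √(0.25×0.75/182.8 + 0.05×0.95/38.2) = 0.0476. Power = Φ(0.20/0.0476 − 1.96) = 98.7%.
- Without dropout (effective n 221.2 and 46.7), unpooled power = 99.6%.
- With pooled variance the two figures are 88.3% and 94.8%.

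The stated 99.4% is thus reproduced to within a point, with unpooled variance only.

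Now suppose, generously, that all 81 had a follow-up test and were spread evenly over the 14 and 3 clinics. Effective n is then 57.7 and 10.4.

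- Pooled test: power about 20%.
- Fisher's exact test, ignoring clustering: about 14%.
- Unpooled test: 62%, which is unreliable with 12 controls.

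These are optimistic illustrations for an earlier visit. At month 12 there are no objective data to analyse.

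**4. The statements on timing, side by side.**

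| Section | Time point |
|---|---|
| Outcomes | every visit, against baseline |
| Statistical methods, model 1 | study end |
| Statistical methods, repeated-measures model | all visits |
| Statistical methods, simple comparison of cessation | none stated |

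Outcomes also spaces its four time points at 3-month intervals, whereas Trial design and Table 1 put the visits at 0, 3, 6 and 12 months.

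**The case against.** The strongest reply is that the trial's main question survives. The Objectives section and the opening sentence of Outcomes define the primary outcome as the cessation rate in intervention versus TAU sites. Item 11 gives a self-reported definition that can be collected by telephone, and the Statistical methods section describes a simple comparison of cessation. The suspension is disclosed in several places, including the limitations in the Discussion. All of this stands, and it confines the finding to aim 1 and Outcomes as worded.

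A reader might infer more, and the document does not support it:

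- *That two abstinence definitions would be mixed.* Item 11 and the Discussion both describe CO corroboration as an original intention. The rule left in force is self-report for everyone, and no month-12 result could be mixed.
- *That cotinine would misclassify quitters who use nicotine replacement.* The corroboration rule used CO, not cotinine, and no cotinine result is available at month 12.
- *That a confidence limit for abstinence among the 12 tested TAU participants shows something.* No visit is given for those tests, so they are not known to be follow-up results.
- *That comparison with baseline is a wrong contrast.* Everyone smokes at entry, so for a binary outcome it reduces to each arm's cessation rate. For CO in ppm, change from baseline would be meaningful.
- *That the type I error is inflated.* Three independent tests at 5% would give 1 − 0.95³ = 14.3%, but the plan nowhere says that success at any visit counts, and Sample size powers a single test.

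**Conclusion.** The finding holds for aim 1 and Outcomes as written. The objective measure they name covers at most 6.75% of planned enrolment and, on the stated dates, nobody at month 12. Aim 1 as worded therefore cannot be answered at study end. This assumes that testing did not restart, as Trial design expects; the repeated description of the stop as temporary contradicts that expectation and should be settled.

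It would be too strong to say that the trial's primary question is unanswerable. The between-arm comparison of cessation remains possible, but it rests on unblinded, unverified self-report.

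The lack of a single primary time point is a conflict between statements in the article, not detail left to an analysis plan. The spacing of visits in Outcomes is a plain inconsistency.

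**What to change.** Amend aim 1 and Outcomes as follows:

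- The single primary endpoint is the between-arm difference in self-reported 7-day abstinence (item 11) at month 12, under one definition for every participant whatever the enrolment date. Month 12 agrees with model 1 and with the visit that the per-protocol set requires.
- Months 3 and 6 become secondary.
- CO and cotinine results from the 81 tested participants are reported descriptively, by visit.
- Remove the word objective from aim 1 and Outcomes, and correct the visit spacing to 0, 3, 6 and 12 months.
- Replace the description of the suspension as temporary with the actual status of testing, consistently across sections.
- State that the primary conclusion rests on unverified self-report in an unblinded trial.

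The cost is a protocol amendment, with a matching registry update if the entry carries the same wording. The claim also becomes weaker: self-reported rather than biochemically supported abstinence. No new data collection or sample size is needed.

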## Trial design {8}

The study design consists of a 5-year implementation, cluster-randomized comparative effectiveness trial comparing intervention clinics with TAU. Intervention clinics provide smoking cessation group counseling and medication management and are integrated into primary care and community mental health clinics. TAU offers information about the California Smoker’s Helpline and usual provider and clinician counseling. Participants in TAU will be asked at each data collection point (baseline, 3, 6, and 12 months) about any smoking cessation services received including prescribed and over-the-counter smoking cessation medication. Each clinical site in LACDHS is part of a cluster, and there will be a 5:1 ratio in the assignment of clinics assigned to the intervention as compared with the TAU. There are eighteen outpatient clinics participating in the study, eleven from LACDHS and seven from LACDMH (see the “Study setting {9}” section for full details of study sites). The present study aims to enroll 1000 participants from the clinics that will offer smoking cessation services and 200 from clinics not offering smoking cessation services. There are four data collection points, baseline, 3 months, 6 months, and 12 months. Each data collection point will take approximately 30–45 min. These interviews will take place at the participant’s primary care clinic or the site associated with where they usually obtain county-provided services.

In the first quarter of year 1, the research team will revise and prepare study material which will include the participant consent forms, participant and clinical staff questionnaires, recruitment documents, and any other related study material. In the second quarter of year 1, year 2, and the first quarter of year 3, the research team will support the implementation of smoking cessation services by providing training to the clinical staff at the intervention site. The research team will meet with the staff at the intervention sites in quarters 2 and 3 of year 1 and quarter 3 of year 2. The intervention will begin in quarter 2 of year 1 and continue through quarter 4 of year 3. The project may continue recruitment if funding remains available.

At the first interview, the researcher will explain the study and answer any questions participants may have. If they agree to participate in the study, they will be enrolled into the study at the first interview. The researcher will then set up a schedule to meet again at 3 months, 6 months, and 12 months. To enhance retention, participants will be asked to provide contact information for the research team to keep in contact for subsequent follow-up interventions.

At each interview, the researcher will complete brief medical and mental health assessments which will ask about participants’ overall physical and mental health, including their smoking status. Data will be collected in-person by the research team via computer-assisted interviews which will include self-reports on smoking history, anxiety, stress, quality of life, and participant satisfaction. Initially, at each interview, we planned on asking participants to complete the carbon monoxide (CO) breathalyzer test and provide a urine sample for the rapid dipstick cotinine test to determine the use of cigarettes and levels of nicotine in the body. The urine collected for this study was to be only tested for cotinine and no other substances. Breathalyzer and urine testing were temporarily suspended in March 2020 in response to the COVID-19 pandemic when enrollment and follow-up assessments shifted from in-person to telephone and in-person visits are not anticipated to resume. Prior to suspension, 12 participants in the TAU arm and 69 participants in the intervention arm completed CO and urine testing.

Participants who are assigned to clinics that provide smoking cessation services will also be asked about the frequency of their participation in the smoking cessation services during the 12-month period. Interviews will be conducted at the participating LAC outpatient clinic where participants receive their primary health care. The smoking cessation services will include a (1) weekly 60–75-min cognitive-behavioral therapy (CBT) smoking cessation counseling group which will be led by facilitators that have been trained through the Kick Ash program and may be a nurse, pharmacist, clinician, substance use disorder (SUD) counselor, behavioral health clinician, or counselor; and (2) smoking cessation medication that will be prescribed by a licensed, prescribing clinician. Smoking cessation medications will include varenicline (Chantix), bupropion (Zyban), and nicotine patches, gum, and lozenges.

